### Secondary outcomes

The secondary clinical outcome measures include the presence of and changes in the following clinical findings: DAS28-CRP remission (DAS28-CRP <2.6) at week 48, ACR/EULAR remission (The 2011 ACR/EULAR Definitions of Remission in Rheumatoid Arthritis Clinical Trials) at week 48 and 96 and DAS28-CRP week 48 and 96.

The secondary imaging outcome measures include the following radiographic and MRI findings: absence of radiographic progression (Sharp/vdHeijde score) from week 0–48 and 48–96 as well as change in the Sharp/vdHeijde score from week 0–48, 0–96 and 48–96. MRI inflammatory and destructive findings are assessed using the semiquantitative OMERACT (Outcome Measures in Rheumatology) scoring system, RAMRIS (RA MRI scoring system) [29]. The following MRI secondary outcomes are assessed: absence of progression in the MRI erosion (RAMRIS) score from week 0–48 and 48–96, change in the MRI erosion (RAMRIS) score from week 0–48, 0–96 and 48–96, MRI synovitis and MRI bone marrow edema (RAMRIS) score at week 48 and 96, and change in DCE-MRI variables [including initial rate of enhancement (IRE) and maximum enhancement (ME)], if available, week 0–48 and 0–96.

Several secondary patient-reported outcomes are assessed. To assess the patients’ physical function, the Health Assessment Questionnaire Disability Index (HAQ-DI) [30] is calculated from the Health Assessment Questionnaire (HAQ). Change in HAQ-DI is calculated from week 0–48 and 0–96. To assess health-related quality of life, the questionnaires Short-Form 36 questionnaire (SF-36) [24,25] and the EuroQol 5 dimension 5 level (EQ-5D-L5) [26] are assessed at baseline and yearly. Changes in the scores are calculated from week 0–48 and 0–96.

For assessment of further secondary outcomes, blood and urine samples will be stored in a biobank for later analysis of various biomarkers.

### Statistics

#### Sample size and power considerations

Primary clinical endpoint: Assuming 60% of patients in the control group and 80% of patients in the intervention group reach the primary clinical endpoint (DAS < 2.6) at month 24, a group size of 64 in each group is needed to give a statistical power of 80% (beta = 0.20) for the detection of statistically one-sided significant (*p* = 0.05) treatment efficacy, assessed on the basis of two independent binomially distributed proportions using Pearson’s chi-square statistics with a chi-square approximation with a one-sided significance level of 0.05. Based on a specified group size of 100 patients in each group (200 in total), the project is assessed as having a 93% chance of success with regard to the clinical efficacy goal (statistical power 0.93).

Primary radiographic endpoint (assessed using the Sharp/vdHeijde score):

Assuming that 75% of patients in the control group^a^ and 90% of patients in the intervention group reach the primary radiographic performance goal (no radiographic progression) at month 24, a group size of 79 in each group is required to give a power of 80% (beta = 0.20) for detection of a statistically one-sided significant (*p* = 0.05) treatment efficacy, assessed on the basis of two independent binomially distributed proportions using Pearson’s chi-square statistics with a chi-square approximation with a one-sided significance level of 0.05. Based on the specified group size of 100 patients in each group (200 in total), the project is assessed as having an 88% chance of success with regard to the radiographic efficacy goal (statistical power 0.879).

Based on “sample size” calculations of the two above-mentioned endpoints, a total sample size of 200 has been selected.

### Statistical analysis plan

The proportion of patients in the two treatment groups who fulfill the primary endpoints will be compared using the chi-square test. This primary analysis will be based on the total intention-to-treat (ITT) population, all randomized patients independent of the adherence to the study protocol. The primary statistical analysis will be based on all usable data, irrespective of protocol deviations, and missing data will primarily be replaced using “multiple imputation” (MI), which assumes that data are ‘missing at random’ [31]. The MI analyses will be based on a “Markov chain Monte Carlo” (MCMC) simulation statement designed to fit Bayesian models to impute values for a data set with an arbitrary missing pattern, assuming a multivariate normal distribution for the data (modeled in SAS). These analyses will secondarily be supplemented by “worst-case” and “best-case” imputation in the event that data are “not missing at random” [32]. With regard to the further hypothesis-generating component of the project, a separate analysis of the patients who adhered to the study protocol (per-protocol analysis) will be carried out.

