**Methods/design:**

The study is a non-blinded, multicenter, 2-year RCT with a parallel group design. Two hundred anti-CCP-positive, erosive RA patients characterized by low disease activity or remission, no clinically swollen joints and treatment with synthetic disease-modifying antirheumatic drugs (DMARDs) will be included. Patients will be randomized to either a treatment strategy based on conventional laboratory and clinical examinations (control group) or a treatment strategy based on conventional laboratory and clinical examinations as well as MRI (intervention group). Treatment is intensified according to a predefined treatment algorithm in case of inflammation defined as a disease activity score (DAS28) >3.2 and at least one clinically swollen joint (control and intervention groups) and/or MRI-detected BME (intervention group only). The primary outcome measures are DAS28 remission (DAS28 < 2.6) and radiographic progression (Sharp/vdHeijde score).

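### The protocol gives each of two primary endpoints the full one-sided 0.05 and never says whether trial success needs both or either

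*Protocol article*

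**What the plan says.** The abstract and the Primary outcomes section name two primary measures: absence of radiographic progression from baseline to week 96 (no increase in total Sharp/van der Heijde score) and DAS28-CRP below 2.6 at week 96. Neither is ranked above the other.

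The section Sample size and power considerations treats them one at a time. For the clinical endpoint: "Assuming 60% of patients in the control group and 80% of patients in the intervention group reach the primary clinical endpoint", which leads to 64 per group for 80% power. For the radiographic endpoint: "Assuming that 75% of patients in the control group" and "90% of patients in the intervention group reach the primary radiographic performance goal (no radiographic progression) at month 24", which leads to 79 per group. Both calculations use a "chi-square approximation with a one-sided significance level of 0.05". At 100 per group, the clinical endpoint is given a "93% chance of success with regard to the clinical efficacy goal (statistical power 0.93" and the radiographic endpoint 88% (0.879). The total of 200 is then chosen on the strength of the two calculations.

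The section Statistical analysis plan states the comparison: "The proportion of patients in the two treatment groups who fulfill the primary endpoints will be compared using the chi-square test". It goes on to the analysis population, multiple imputation, worst-case and best-case imputation, and a per-protocol analysis. It gives no significance level, no division of alpha, no testing order and no definition of trial success.

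**The concern.** With two primary endpoints, the error rate and the power of the trial depend on what counts as success. The protocol leaves that open while giving each endpoint the whole 0.05. Two readings are possible, and the printed figures do not describe the trial under either.

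- **Either endpoint suffices.** There are two chances of a false claim, each at 0.05, and the family-wise error exceeds 5%.
- **Both endpoints are needed.** The error rate is controlled, but 93% and 88% are the powers of the components. The chance that the trial succeeds is lower and is not stated.

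The choice has practical weight here. Patients and investigators know the allocation, and DAS28-CRP contains joint counts and the patient's global assessment. The radiographs are scored by readers blinded to arm. With no rule, a positive claim could rest on the endpoint open to influence while the blinded one fails. If the rule is chosen after the results are known, it protects neither error rate nor credibility.

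**Working it through.** **Inputs from the protocol.** Clinical rates 0.60 and 0.80; radiographic rates 0.75 and 0.90; one-sided alpha 0.05 for each; 100 per group, allocated 1:1. The documents give no correlation between the two test statistics, so correlations below are assumptions.

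**1. Reproduce the stated figures.** Pooled-variance formula without continuity correction, where p̄ is the mean of the two rates p₁ and p₂, and d is their difference:

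n = [z(1−α)·√(2p̄(1−p̄)) + z(0.80)·√(p₁(1−p₁)+p₂(1−p₂))]² / d²

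- Clinical: [1.645·√0.42 + 0.842·√0.40]² / 0.04 = 63.9, so 64.
- Radiographic: [1.645·√0.28875 + 0.842·√0.2775]² / 0.0225 = 78.3, so 79.

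Power = Φ{[d·√n − z(1−α)·√(2p̄(1−p̄))] / √(p₁(1−p₁)+p₂(1−p₂))} at n = 100:

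- Clinical: Φ(1.477) = 0.9301 (stated 0.93).
- Radiographic: Φ(1.170) = 0.8789 (stated 0.879).

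All four figures match. Two-sided 0.05, or equally one-sided 0.025, would need 82 and 100 per group. The continuity-corrected one-sided versions need 74 and 92. The plan therefore did use the full one-sided 0.05 for each endpoint.

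**2. Either endpoint suffices.** With no effect on either endpoint and independent tests, the chance of at least one false positive is 1 − 0.95² = 0.0975. With correlated statistics (bivariate normal):

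| Assumed correlation | Family-wise one-sided error |
|---|---|
| 0 | 9.75% |
| 0.3 | 9.29% |
| 0.5 | 8.78% |
| 0.7 | 8.04% |
| 0.9 | 6.81% |

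The bound under any dependence is 0.05 + 0.05 = 10%.

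**3. Both endpoints needed.** Joint power under independence is 0.9301 × 0.8789 = 0.8175. At assumed correlations of 0.3, 0.5 and 0.8 it is 0.828, 0.837 and 0.858. It cannot fall below 0.9301 + 0.8789 − 1 = 0.809 under any dependence, nor exceed 0.879.

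**4. Holm at family-wise one-sided 0.05.** An endpoint is rejected if its p-value is at most 0.025, or if it is at most 0.05 and the other's is at most 0.025. Power at one-sided 0.025 with 100 per group is 0.8757 (clinical) and 0.8018 (radiographic). Under independence:

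- Clinical: 0.8757 + (0.9301 − 0.8757) × 0.8018 = 0.919.
- Radiographic: 0.8018 + (0.8789 − 0.8018) × 0.8757 = 0.869.

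The losses against the plan's figures are 93.0 − 91.9 = 1.1 points and 87.9 − 86.9 = 1.0 point.

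**The case against.** The strongest defence has three parts.

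*The analysis section gives no alpha.* This is correct. The 0.05 comes from the power calculation, so a reader who says the plan tests each endpoint at full alpha is making an inference. It is a reasonable one, because the stated sample sizes and powers come out only at that level, but the sentence on the chi-square test does not say it.

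*The aim joins the two goals.* The Background speaks of preventing erosive progression and increasing the remission rate. If that means both must be shown, there is no inflation, and 100 per group still gives about 82% joint power. This stands as a possible reading. It is an aim rather than a decision rule, however, and the sample size section describes success separately for each goal.

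*This is a condensed article, and a fuller plan could hold the rule.* That is possible, and the gap alone would not be a finding. The article does more than stay silent, though: it fixes the alpha and prints a chance of success for each endpoint. A later split of alpha would contradict those powers, and a both-must-succeed rule would make neither of them the trial's chance of success. Only a fixed testing order would leave one of the two figures intact, and none is stated.

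A reader might go further and conclude that the trial runs at double its stated error rate. The documents do not support that. It requires the either-endpoint reading, which the protocol never adopts, no true effect on either endpoint, and tests that are not strongly correlated.

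**Conclusion.** The point holds as an undefined success rule combined with full alpha for each of two primary endpoints. It does not establish that the trial's error rate is inflated.

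Under the either-endpoint reading, the family-wise one-sided error is 9.75% with independent tests, falling to 8.8% and 6.8% at assumed correlations of 0.5 and 0.9, with a ceiling of 10%. These figures apply when neither endpoint is affected by the strategy. Under the both-endpoints reading, the error rate is sound and the correction is to the stated power: about 82% under independence and at least 80.9% under any dependence. All power figures rest on the protocol's assumed rates and 100 analysable patients per group.

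The sample size is not in question under either reading. The rule decides what the trial may claim on its primary outcomes, so it needs to be fixed before analysis. The trial was still recruiting when the article was written.

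**What to change.** State the success rule in the Statistical analysis plan section before any analysis, and bring the sample size section into line. Either of the following would do:

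- **(a) Separate claims.** Test the two endpoints with Holm's procedure at the plan's own family-wise one-sided 0.05, and make a claim only for an endpoint that is rejected. Restate power at 100 per group as about 92% (clinical) and 87% (radiographic), assuming independence.
- **(b) Both required.** Declare success only if both endpoints are significant, each at one-sided 0.05. State joint power of about 82%, assuming independence.

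The cost is one paragraph. Option (a) gives up about 1 point of power per endpoint. Option (b) gives up no alpha but replaces 93% and 88% with a less favourable headline figure. N = 200 is unchanged in both.

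Whether testing should be one-sided or two-sided is a separate decision and not part of this change. Making both changes together would obscure the cost: Holm at family-wise two-sided 0.05 gives 85.6% and 78.5%, and most of that fall comes from the sidedness, not from handling two endpoints.

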### Procedures

During the 2-year study period, the patients will have seven visits in the outpatient clinic with 4-month intervals (see Figure 2). The time from the screening visit to inclusion should not exceed 4 weeks. An overview of visits and corresponding assessments is shown in Table 1. If the patient is excluded/withdrawn from the study, the patient is asked to attend follow-up visits at the time points for visits 4 and 7 (years 1 and 2) having the related procedures performed.

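### For data not missing at random the article names only worst-case and best-case imputation, undefined by arm; read as opposing extremes, the pair says little from about 15% missing

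*Protocol article*

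**What the plan says.** All quotes are from the protocol article. The Statistical analysis plan section sets the comparison, "The proportion of patients in the two treatment groups who fulfill the primary endpoints will be compared using the chi-square test", and the population: "This primary analysis will be based on the total intention-to-treat (ITT) population, all randomized patients independent of the adherence to the study protocol". On missing outcomes it states: "missing data will primarily be replaced using “multiple imputation” (MI), which assumes that data are ‘missing at random". For departures from that assumption it offers one supplement: "These analyses will secondarily be supplemented by “worst-case” and “best-case” imputation in the event that data are “not missing at random".

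The section does not assign outcomes to missing patients by arm. It sets no criterion for reading the two results and names no graded scenario. The per-protocol analysis it also mentions belongs to the hypothesis-generating part of the project.

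Two other sections bear on the point. Sample size and power considerations gives the planned rates and 100 patients per group, but no expected missing share. Procedures describes how withdrawn patients are followed: "If the patient is excluded/withdrawn from the study, the patient is asked to attend follow-up visits at the time points for visits 4 and 7".

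**The concern.** Outcome-related missingness is plausible here. Patients and investigators know the allocation, follow-up lasts two years, withdrawn patients are asked rather than certain to return, and DAS28-CRP includes the patient's own global score. A sensitivity analysis should show how far the data can depart from missing at random before the conclusion changes.

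Opposing extremes do not show this once more than a few patients are missing. The distance between best and worst case is fixed by the number missing, not by the treatment effect. When it is as large as the planned effect, the usual result is a significant best case and a non-significant worst case, whether or not MRI guidance works. The trial could then report a favourable primary result without being able to say whether it survives a realistic departure from the assumption.

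**Working it through.** **Inputs from Sample size and power considerations.** Remission: "Assuming 60% of patients in the control group and 80% of patients in the intervention group reach the primary clinical endpoint". No radiographic progression: "Assuming that 75% of patients in the control group", against 90% with MRI guidance. 100 per group, Pearson chi-square, one-sided 0.05.

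**Assumption.** Missing share m per arm of 5, 10, 15 or 20%, equal in both arms and unrelated to outcome.

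**Step 1: reproduce the plan's figures.** With d the difference in rates and p̄ their mean,

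n = [1.645·√(2p̄(1−p̄)) + 0.842·√(pC(1−pC) + pI(1−pI))]² / d².

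- Remission: (1.066 + 0.532)² / 0.04 = 63.9, so 64, as stated. Power at 100: Φ((2.0 − 1.066)/0.632) = 0.930; stated 0.93.
- Radiographic: (0.884 + 0.443)² / 0.0225 = 78.3, so 79. This agrees with "a group size of 79 in each group is required to give a power of 80" per cent. Power at 100: Φ((1.5 − 0.884)/0.527) = 0.879; stated 0.879.

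**Step 2: expected difference under opposing extremes.**

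- Worst case (missing MRI-group patients fail, missing controls succeed): (1−m)d − m.
- Best case (the reverse): (1−m)d + m.

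The gap between them is 2m whatever d is. At m = 0.15 the worst-case difference is 0.85 × 0.20 − 0.15 = +0.02 for remission and 0.85 × 0.15 − 0.15 = −0.02 for the radiographic endpoint. With no effect, the best case shows +0.15. The worst-case difference reaches zero at m = d/(1+d): 0.20/1.20 = 16.7% for remission and 0.15/1.15 = 13.0% for the radiographic endpoint.

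**Step 3: how often each bound is significant in favour of MRI.** Simulated trials of 100 per arm, missing counts Binomial(100, m), pooled z > 1.645. No effect means both arms at the control rate. With nothing missing the simulation gives 93% and 88.5%, in line with Step 1.

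| Missing per arm | Worst case, planned effect: remission | Worst case, planned effect: radiographic | Best case, no effect: remission | Best case, no effect: radiographic |
|---|---|---|---|---|
| 5% | 70% | 51% | 18% | 20% |
| 10% | 34% | 15% | 42% | 48% |
| 15% | 9% | 2% | 70% | 77% |
| 20% | 1% | 0.2% | 89% | 93% |

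**Step 4: read the two bounds together.** A split means the best case is significant and the worst case is not.

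- At 5%, the worst case is significant in under 1% of trials with no effect, against 70% and 51% with the planned effect. The pair discriminates.
- At 10%, with exactly 10 missing per arm, both bounds are non-significant in 59% (remission) and 52% (radiographic) of trials with no effect, but in about 0.2% with the planned effect. The pair discriminates in part.
- At 15%, a split occurs in 70% (no effect) against 91% (planned effect) for remission, and 77% against 98% for the radiographic endpoint.
- At 20%, the figures are 89% against 99%, and 93% against almost 100%.

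**Step 5: the other reading.** If every missing patient in both arms is given the same outcome, the expected difference is (1−m)d, which stays at zero when there is no effect. With exactly 20 missing per arm, the test favours MRI in 2–4% of trials with no effect. With the planned effect it does so in 79–86% (remission) and 59–81% (radiographic). Discrimination is kept, but missingness that differs between arms is not examined.

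**Step 6: what a graded analysis would show.** This is a normal approximation that ignores imputation variance. At 15% missing and the planned effect, significance is lost when the success rate of missing MRI-group patients falls about 60 points (remission) or 38 points (radiographic) below that of observed ones: 0.80 − 0.15 × 0.60 = 0.71 against 0.60, and 0.90 − 0.15 × 0.38 = 0.843 against 0.75. If missing MRI-group patients are instead given the control rate, power at 20% missing is still 0.79 and 0.70.

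**The case against.** The strongest reply is that nothing here decides the trial. The bounds are a secondary supplement, the article attaches no pass or fail rule to them, and a best case is meant to favour the intervention. A reader might infer that the plan would declare a true effect not robust, or that the best case inflates the trial's false-positive rate. The article supports neither: the claim of efficacy rests on the chi-square test with multiple imputation. This part of the reply stands.

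A reader might also infer that the pair fails at ordinary levels of missingness. That does not stand either. No missing share is given, the bounds still work at 5% and partly at 10%, and the failure needs the opposing-arm definition, which the article does not state. Nor is the margin between 79 needed and 100 planned a dropout allowance, because the stated powers use all 100 per group. Asking withdrawn patients back and sending electronic queries for missing data should also keep losses down.

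Finally, tipping-point detail is often left to a separate analysis plan, and one may exist. The article does, however, state a method for data not missing at random and leaves its meaning open. Under one natural reading, that method answers the question poorly at the trial's own effect sizes.

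**Conclusion.** The point holds conditionally. The article leaves worst and best case undefined by arm and names no intermediate scenario. Under opposing extremes, the pair is largely uninformative from about 15% missing per arm and almost fully so at 20%; below that it keeps some or most of its value. Under the same-outcome reading it discriminates but does not examine arm-specific missingness.

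This rests on the planned rates, 100 per arm, one-sided 0.05, and assumed equal missing shares of 5–20%. It applies to what this article names, not to any fuller plan. The primary analysis and its error rate are not in question. It is a worthwhile, inexpensive improvement rather than a defect in the main comparison.

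**What to change.** State which outcome missing patients in each arm receive in the worst case and in the best case. Add a delta-adjusted (tipping-point) multiple imputation for both primary endpoints. It should vary the imputed probability of success separately in the MRI and control groups, report the shift at which significance is lost, and comment on whether that shift is clinically plausible. Keep worst and best case as the end points of that range rather than as a test of robustness.

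The cost is a change of wording and a few extra imputation runs on data already collected, with no added patients or procedures. The drawback is a grid of results to report in place of two figures.

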### Data registration and monitoring

The IMAGINE-RA study is carried out in accordance with the approved protocol and the applicable regulatory requirements and legislation in this field. A good clinical practice (GCP) monitoring plan has been developed in cooperation with the GCP unit in Copenhagen to ensure that the trial is carried out, registered and reported in accordance with the protocol, with specified procedures and with Danish law. Two internal monitors who will ensure that all data have been entered correctly and in accordance with the protocol will carry out monitoring. If data are missing, queries will be sent electronically to the sites. All study information will be recorded in the e-CRF, which is developed to function within the Danish DANBIO registry. The e-CRFs will be completed by the investigator, project nurse and patient. To get access to the e-CRF, a username and password are required.

